### Data Collection

All data are collected using paper versions, and are then entered and recorded on a secure server (Table 1).

All questionnaires are completed at each measuring point of the study for each patient. Questionnaires have been selected on the basis of ease and speed of administration by an interviewer, peer-validated, and on the fact that they are the most widely used questionnaires in this type of research (see Multimedia Appendix 1).

Saliva sampling has been performed according to a standardized methodology (see Multimedia Appendix 2).

**Table 1 table1:** Summary of data collection.

Data type	Qualitative data	Quantitative data
Thyroid cancer information (collected only at the enrollment visit)	Size of the postsurgery remnant, tumor histology, pTNM^a^ staging, Tg^b^ stimulation protocol, family history of thyroid cancer, patient history of cancer or comorbidities, prescribed activity of ^131^I (1.1 or 3.7 GBq)	Surgery to therapy duration (months)
Clinical data	Self-rated menopausal status, all medications used during the last 3 months, tobacco and alcohol consumption, self-palpation of the salivary glands (normal, painful, or swollen), self-reported oral carries or infections, observed cracked lips, self-reported use of a saliva substitute, sialagogue	Age, height, weight
Questionnaires	Salivary complaints questionnaire; eye dryness, OSDI^c^ questionnaire; questions about nutrition; anxiety and depressive symptoms (HAD^d^ scale)	Physical and mental composite scores about quality of life (MOS SF-36^e^)
Saliva samples	Not applicable	Weight (precision 0.01 mg), volume (precision 0.01 mL), electrolyte concentrations (mmol/L: sodium, potassium, chloride, amylase, and total protein composition), genetic and epigenetic variant proportions

^a^pTNM: pathological tumor-node-metastasis.

^b^Tg: thyroglobulin.

^c^OSDI: Ocular Surface Disease Index.

^d^HAD: Hospital Anxiety and Depression.

^e^MOS SF-36: Medical Outcome Study Short Form 36 items.

### Dosimetry

Immediately before therapy, three thermoluminescent dosimeters (^7^LiF: Mg,Ti, Thermo Scientific DXT-RAD dosimeter model: DXT-700, provider: APVL) are placed under each earlobe (at the salivary glands level) and at the sternal fork level, protected by an adhesive plastic film (Figure 2). They are removed 5 days later, just before the posttherapy scan.

**Figure 2 figure2:**
[figure not shown]
Thermoluminescent dosimeter position.

Subsequently, the dose received specifically by the salivary glands will be estimated from the dosimeter readings. This requires the development of a specific calibration protocol that allows relating the dosimeter readings to the cumulative activity in the salivary glands and thyroid residues, using computational human models [17]. To validate this method, the response of thermoluminescent dosimeters to iodine does not have to deviate significantly from their response under standard calibration conditions.

### Study Endpoints

#### Primary Endpoint

The primary endpoint is a composite criterion combining objective (salivary flow dysfunctions with and/or without stimulation) and subjective (reporting discomfort, pain in the parotid area, difficulty swallowing, or eye dryness) criteria at T6. Salivary flow dysfunctions are defined as an unstimulated salivary flow <0.2 mL/min and/or a stimulated salivary flow <0.7 mL/min [18,19].

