Finally, while a strong interrelationship between epigenetic processes and genetic factors associated with dry mouth syndrome has been shown [14], the potential existence of individual genetic sensitivity to ^131^I in mediating the relationship between ^131^I exposure and salivary dysfunctions is important to study, especially as specific epigenetic changes could lead to increased sensitivity to ionizing radiation [15]. Other risk factors of salivary dysfunctions in the context of thyroid cancer treated by ^131^I-therapy are poorly understood. Only one study investigated the relationship between salivary flow and age, gender, or pathological tumor-node-metastasis (TNM) staging, but did not show any significant relationship, potentially owing to a lack of statistical power due to the small number of patients included (N=67) [11], emphasizing the importance of setting up a study with a large number of patients. Increased knowledge of these factors would help to identify the patients at risk of developing salivary dysfunctions, which could possibly help to adapt the treatment and follow-up accordingly.

In this context, the Salivary dysfuncTions After Radioiodine Treatment (START) study was launched in September 2020, with the following objectives: (1) to estimate the mid- and long-term incidence of salivary dysfunctions in patients with thyroid cancer treated with ^131^I, using objective, subjective, and mixed criteria; (2) to highlight risk factors of posttreatment salivary dysfunctions using clinical, pathological, biomolecular, and biochemical factors; (3) to validate a dosimetric method to calculate the dose absorbed by the salivary gland; (4) to estimate the dose-response relationship between exposure of the salivary glands to ^131^I and salivary dysfunctions; and (5) to investigate the consequences of salivary dysfunctions on the quality of life and nutritional status of patients.

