## Methods

### Study Design

START is a prospective self-controlled study that includes patients with thyroid cancer who underwent thyroidectomy and are candidates for complementary ^131^I-therapy. This research program aims to enroll 120 patients from the nuclear medicine department of Pitié-Salpêtrière Hospital (Paris, France), divided into two groups of 40 and 80 patients treated with ^131^I activity of 1.1 GBq and 3.7 GBq, respectively, thus expecting a high number of patients with salivary dysfunctions to provide good statistical power for the analyses.

All consecutive patients awaiting ^131^I-therapy are systematically invited to participate in the study. They are enrolled just prior to the ^131^I capsule administration (ie, 1 to 3 months after thyroidectomy), and have three follow-up points: at enrollment (T0), and at 6 months (T6) and 18 months (T18) after ^131^I-therapy (Figure 1).

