**Adjustment factors to be tested**
Gender, self-rated menopausal status, age, BMI, histology, thyroid remnant tissue, pathological tumor-node-metastasis staging, thyroglobulin stimulation protocol, salivary comorbidities, medication intake, tobacco and alcohol consumption, surgery to therapy duration (months), family history of thyroid cancer

All statistical analyses will be performed using SAS statistical software for Windows (SAS Institute, Cary, NC). An α level of .05 will be accepted as significant.

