## Results

Patient enrollment took place from September 2020 to April 2021, with a total of 139 patients enrolled, including 45 and 94 patients treated with 1.1 and 3.7 GBq ^131^I, respectively.

Characteristics of the study participants are displayed in Table 2. The START sample is composed of a large majority of women, with an average age of 47 years (range 18.70-81.80 years). All patients underwent total thyroidectomy with a diagnosis of differentiated thyroid cancer confirmed by pathological examination; the highest proportion in the TNM classification was Tx-T2, followed by Nx-N0, N1, T3, and T4, including approximately 47% of patients with residual thyroid tissue. The ^131^I-therapy was performed an average 4.11 (SD 3.91) months after the surgery (range 1-35 months). The majority of the included patients were treated for a papillary thyroid cancer.

Concerning the saliva samples, the mean pH was 7.34 (SD 0.48; range 6.00-8.50), with flow rates of 0.76 (SD 0.46; range 0.04-3.00) mL/min and 2.13 (SD 0.88; range 0.40-4.82) mL/min for unstimulated and stimulated saliva, respectively.

Statistically significant differences between the 1.1 and 3.7 GBq treated groups were found in saliva pH and nonstimulated saliva volume.

At the enrollment visit, among all 139 patients, 19 (13.6%) patients had suspicious or obvious symptoms of depression, whereas 67 (48.2%) patients had suspicious or obvious symptoms of anxiety according to the Hospital Anxiety Depression scale (see Table S1 in Multimedia Appendix 3).

When asked if patients experienced changes after thyroid removal surgery, 25 (18.0%) had the sensation of a dry mouth, 48 (34.5%) said they drink more often, and 27 (19.4%) were eating less salty foods.

Regarding lifestyle habits, among the 139 patients, 95 (68.3%) had never smoked, compared to 28 (20.1%) exsmokers and 16 (11.5%) current smokers; 87 (62.6%) never drink alcohol, compared to 45 (32.4%) being occasional drinkers (1-7 drinks/week) and 7 (5.0%) being regular drinkers (7-14 drinks/week) (see Table S1 in Multimedia Appendix 3).

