Unstimulated saliva flow (mL/min), mean (SD)			3.13 (1.82)		4.12 (2.47)		3.8 (2.32)		.02
Stimulated saliva flow (mL/min), mean (SD)			9.65 (3.18)		11.12 (4.83)		10.65 (4.41)		.07
**Dry mouth sensation after treatment, n (%)**									.67
	Yes	9 (20)		16 (17)		25 (18.0)			
	No	36 (80)		78 (83)		114 (82.0)			
**Saliva pH, mean (SD)**			7.2 (0.42)		7.41 (0.50)		7.34 (0.48)		.02
**Dry eye (OSDI^f^), n (%)**									.29
	Normal	34 (79)		78 (86)		112 (83.6)			
	Light	3 (7)		8 (9)		11 (8.2)			
	Mild	4 (9)		2 (2)		6 (4.5)			
	Severe	2 (5)		3 (3)		5 (3.7)			

^a^*P* values are based on the *t* test for continuous variables or the *χ*^2^ test for categorical variables.

^b^pTNM: pathological tumor-node-metastasis.

^c^TSH: thyroid-stimulating hormone.

^d^rTSH: recombinant thyroid-stimulating hormone.

^e^RAI: radioactive iodine.

^f^OSDI: Ocular Surface Disease Index.

**Table 3 table3:** Dosimetry description.

Variables	1.1 GBq group (n=45)	3.7 GBq group (n=94)
Recorded doses at the left earlobe [Hp(0.07), mSv], mean (SD)	30.07 (9.81)	104.38 (35.43)
Recorded doses at the right earlobe [Hp(0.07), mSv], mean (SD)	30.74 (8.88)	107.72 (42.66)
Recorded doses at the sternal fork [Hp(0.07), mSv], mean (SD)	49.88 (31.47)	173.33 (94.2)
Absorbed doses to the salivary glands (mGy), mean (SD)^a^	702.00 (310.00)	2316.00 (784.00)

^a^N=127.

Further results should be published in 2022. These will be based on comparisons of data from questionnaires and saliva samples between T0 and T6. Individual factors associated with salivary dysfunctions will be presented, as well as the dose-response relationship between absorbed doses to the salivary glands and salivary dysfunctions at T6 and T18.

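### The primary composite is T6 status with no T0 condition, and the adjustment list omits the T0 outcome, so dysfunction already present before 131I would count towards incidence

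*Protocol article*

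**What the plan says.** - **Aim.** The first objective in the Introduction is "to estimate the mid- and long-term incidence of salivary dysfunctions in patients with thyroid cancer". Planned Analyses describes the multivariable models as measuring the risk that dysfunction develops. Study Design states: "START is a prospective self-controlled study that includes patients with thyroid cancer".
- **Primary endpoint.** It combines flow and symptoms. For flow: "Salivary flow dysfunctions are defined as an unstimulated salivary flow <0.2 mL/min and/or a stimulated salivary flow <0.7 mL/min". The symptom part ends with "difficulty swallowing, or eye dryness) criteria at T6". Neither part refers to T0. By contrast, several secondary endpoints are written as changes from T0.
- **Eligibility.** The exclusions concern previous or repeated 131I only. Pre-existing salivary or lacrimal dysfunction is not an exclusion.
- **Models.** Textbox 1 lists the composite as categorical, with chi-square, logistic and Poisson methods. The mixed model appears only under continuous outcomes. Paired tests compare T0 with T6.
- **Adjustment factors.** The list begins "Gender, self-rated menopausal status, age, BMI, histology, thyroid remnant tissue". It contains no T0 flow, T0 symptom or T0 composite value. The nearest item is salivary comorbidities. Factors enter the multivariable models through a 10% univariate screen.
- **T0 data (Results).** All-patient "flow rates of 0.76 (SD 0.46; range 0.04-3.00) mL/min and 2.13 (SD 0.88; range 0.40-4.82) mL/min" for unstimulated and stimulated saliva. Also, "25 (18.0%) had the sensation of a dry mouth". Table 2 shows 22 of 134 with an abnormal OSDI grade, 7 of 139 with a history of salivary dysfunction, and one patient with Sjögren syndrome.

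**The concern.** Incidence counts new cases among people free of the condition at the start. Status at T6 counts everyone who meets the criterion then, including those who met it before 131I. Cases that 131I cannot have caused also add a roughly equal amount to both activity groups, which pulls the contrast between them towards no difference.

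The second half of the point is adjustment. The groups are not randomised, and T0 unstimulated flow is higher in the 3.7 GBq group. A T6 model without the T0 value carries that head start into the activity comparison, where it may mask an effect of the higher activity. The two places where T0 is used do not repair the composite: paired tests do not compare the groups, and the mixed model is listed for continuous outcomes only.

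**Working it through.** **1. Are there T0 cases?** The T0 minima are 0.04 mL/min (cut-off 0.2) and 0.40 mL/min (cut-off 0.7), so at least one patient lies below each cut-off. Eye dryness is a named component, and abnormal OSDI at T0 is (11+6+5)/134 = 16.4%. Dry mouth is 25/139 = 18.0%, but it is not a named component and serves only as a proxy.

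The share with low flow is not reported. From the unstimulated mean 0.76 and SD 0.46, the share below 0.2 is 1.7% under a lognormal shape and 11.2% under a normal shape. For stimulated flow (2.13, SD 0.88) the share below 0.7 is 0.5% to 5.2%. These are distributional estimates, not data.

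**2. Baseline imbalance.** Table 2, row "Unstimulated saliva flow (mL/min), mean (SD": 3.13 (SD 1.82, n=45) against 4.12 (SD 2.47, n=94). Pooled SD 2.28; SE = 2.28 × √(1/45+1/94) = 0.414; t = 0.99/0.414 = 2.39; P = 0.018, which matches the stated .02. For stimulated flow, recomputed P = 0.066 (stated .07).

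Table 2 means are five times the flows in the text (3.8/0.76 = 5; 10.65/2.13 = 5). Assuming that they are 5-minute volumes, unstimulated flow is 0.63 against 0.82 mL/min, a difference of 0.20. In a T6-only flow regression, the carry-over is this difference times the T0-T6 correlation. That correlation is not given; at 0.3, 0.5 and 0.7 the carry-over is 0.06, 0.10 and 0.14 mL/min.

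**3. The plan's sample size.** For 30% against 60% at 1:2, two-sided 5%, 80% power, the pooled formula gives 32+64 = 96, or 37+74 = 111 with continuity correction. The stated 40+80 = 120 is not reproduced, but it errs on the safe side. Power at 40/80 = Φ[(Δ − 1.96·SE₀)/SE₁], with Δ = 0.30, SE₀ = √(0.25 × 0.0375) = 0.0968 and SE₁ = √(0.21/40 + 0.24/80) = 0.0908. This gives Φ(1.21) = 88.8%. The point here does not rest on the stated 120.

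**4. Effect of T0 cases.** Assume that 30% and 60% are new-onset risks p and that a share b meets the criterion at T0 and still does at T6. T6 prevalence is then b + (1−b)p. For b = 0.164: 0.164 + 0.836 × 0.30 = 41.5% and 0.164 + 0.836 × 0.60 = 66.6%.

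| T0 rate b | T6 prevalence, 1.1 / 3.7 GBq | Difference | Power, T6 status, 40/80 | Power, free at T0 |
|---|---|---|---|---|
| 0 | 30.0% / 60.0% | 30.0 points | 88.8% | 88.8% |
| 2% | 31.4% / 60.8% | 29.4 | 87.3% | 88.1% |
| 5% | 33.5% / 62.0% | 28.5 | 85.0% | 87.1% |
| 11% | 37.7% / 64.4% | 26.7 | 79.9% | 84.8% |
| 16.4% | 41.5% / 66.6% | 25.1 | 75.0% | 82.4% |
| 18% | 42.6% / 67.2% | 24.6 | 73.6% | 81.6% |

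The last column uses 40(1−b) and 80(1−b) patients. At the enrolled 45/94, before losses, T6 status gives 80.5% (b = 16.4%) and 79.1% (b = 18%). The odds ratio falls from 3.5 at b = 0 to 2.8 at b = 16-18%.

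**The case against.** **The T0 rate of the endpoint is unknown.** A reader might infer from the dry-mouth and dry-eye figures that 16-18% are composite cases at T0 and that power is really 74-75%. The article does not support that as a finding. It needs a rule under which one symptom alone suffices. The text speaks of combining objective and subjective criteria and elsewhere of a sum of dysfunctions, so the rule is not fixed as either/or. If both parts are required, the T0 rate cannot exceed the share with low flow. Taking the unstimulated estimate of 2-11%, power stays at about 80% or more. This objection stands, which is why a range is shown.

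**Persistence and the planning rates are assumptions.** T0 symptoms were asked as changes since surgery, and 49 of 94 patients in the 3.7 GBq group but none of 45 in the other had thyroid hormone stopped before treatment, so T0 may not be a steady baseline. If only half of an 18% T0 share persists (b = 9%, the rest carrying the new-onset risk), power at 40/80 is about 82%. If the 30% and 60% are themselves post-treatment prevalences, T6 status matches the planning basis and no planned power is lost. Both points stand against the power figures, but not against the mismatch between T6 status and incidence.

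**T0 is not ignored.** Mixed models are planned for continuous outcomes, which include flow, and Results announces T0-T6 comparisons. So the 0.06-0.14 mL/min carry-over concerns only a T6-only flow regression, and it cannot be said that the baseline imbalance passes into every flow analysis. The composite remains uncovered.

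**An analysis plan may say more.** It may, but the endpoint and the adjustment list are stated here, and it would have to change them.

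**T6 follow-up is complete.** Replacing the primary endpoint now would be a late change, not mere wording. This stands and shapes the fix.

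**Conclusion.** The point holds for the primary composite. As written, it measures prevalence at T6, while the stated aim is incidence. Patients who met the criterion before 131I would count as cases after it, and the listed T6 models for the composite do not include T0 status. T6 status would overstate incidence insofar as T0 cases persist, and it would tend to dilute the contrast between activities.

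The size cannot be fixed from the article. Under the assumptions in the working, T0 rates of 2%, 5%, 11% and 16-18% give power at 40/80 of about 87%, 85%, 80% and 74-75%, against 88%, 87%, 85% and 82% among patients free of dysfunction at T0. At 45/94, T6 status still gives 79-81% for T0 rates of 16-18%.

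Two stronger readings go too far. One is that the study already reports prevalence as incidence: no T6 outcome is shown, so this is what the plan would produce. The other is that the baseline imbalance hides harm at 3.7 GBq: its direction means that it may mask an activity effect in T6-only models, and no more can be said.

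**What to change.** 1. Force the T0 value of the same outcome into every T6 model, whatever the 10% univariate screen shows: T0 status for the composite and other categorical outcomes, and ANCOVA for flow, pH and electrolytes.
2. Estimate incidence as the criterion met at T6 among patients who did not meet it at T0, and report T0 and T6 prevalence beside it, by activity group.
3. Keep the T6 composite as the protocol states it, but call it prevalence. Document the incident-case analysis as an amendment dated before the outcome analysis, because T6 follow-up is complete.

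**Cost.** No new data are needed: flow, symptoms and saliva chemistry were collected at T0. The work is an amendment and additional analyses. The at-risk set is smaller (by 16-18% in the least favourable scenario shown), the incidence figure will be lower, and patients who worsen from an already abnormal T0 drop out of the incidence estimate. The adjusted models in all patients keep those patients.

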#### Secondary Endpoints

Secondary endpoints are defined as follows: change in quality-of-life score between T0, T6, and T18; change in nutrition between T0, T6, and T18; change in chemical saliva composition between T0 and T6; change in anxiety and depression symptoms between T0, T6, and T18; genetic and/or epigenetic variant identification that may modify the risk of salivary dysfunctions after ^131^I-therapy; identification of individual factors associated with salivary dysfunctions at T6 and T18; and dose-response analysis between the ^131^I-dose received precisely at the salivary glands and salivary dysfunctions at T6 and T18.

### Statistical Analyses

#### Sample Size Calculation

A minimum of 120 patients is required to complete the START study. This number is based on a statistical power of 80% with an α risk of 5%, and with theoretical percentages from the literature of salivary dysfunctions of 30% and 60% for the 1.1 GBq and 3.7 GBq therapy groups, respectively [4,20,21]. Thus, the number of patients required is distributed as follows: 40 and 80 patients in the groups treated with delivered activities of 1.1 GBq and 3.7 GBq, respectively. Furthermore, to consider potential losses during follow-up, a final number of 130 patients is required.

#### Descriptive Analyses

The description of the population (means, SDs, and percentages) at baseline (before ^131^I-therapy) is presented in this paper. Comparison tests have been performed (*t* test and *χ*^2^ tests) between the two groups of patients (1.1 GBq and 3.7 GBq groups) at T0. This is based on medical and individual data collected in the questionnaire, the ^131^I dose received precisely at the salivary glands in comparison with the delivered activity, saliva flow descriptions, and responses to the questionnaires.

#### Planned Analyses

Paired comparison tests will be used to assess differences in data between T0 and T6. Correlations, principal component analyses, and multiple correspondence analyses will be used to study the factors (objective and subjective) common to patients with salivary dysfunctions after ^131^I-therapy.

All factors significant at a 10% threshold in univariate analyses using different regression models (Textbox 1) will then be entered into multivariate models to measure the risk of developing salivary dysfunctions or other outcomes, adjusted for risk factors previously identified.

The mixed regression models, adjusted for confounders, performed to investigate the temporal evolution for the different outcomes, will be set up using a random intercept for each patient with a first-order autoregressive covariance structure to account for repeated measurements.

The different scores to the questionnaires for quality of life, nutrition, and symptoms of depression and anxiety assessments are calculated and classes are created according to the recommendations for each questionnaire and for each visit (T0, T6, and T18).

Synthesis of the planned analyses.

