#### Enrollment Visit (T0)

The enrollment visit occurs when an eligible patient has given consent to participate in the study. This visit takes place at the hospital during the consultation prior to the complementary ^131^I-therapy (on the day of treatment, approximately 2 months after surgery) in a face-to-face manner with a clinical research associate. Clinical and personal data and saliva samples are collected, self-administered questionnaires are provided to patients (see Data Collection section below and Multimedia Appendix 1), and the patients are equipped with thermoluminescent dosimeters (see Dosimetry section below) just before administration of the ^131^I-therapy. The dosimeters will be removed by the physician 5 days later, immediately before the posttherapy scan.

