Regarding radioiodine activity, the average doses recorded by the thermoluminescent dosimeters are presented in Table 3. Preliminary results based on the numerical calibration of the dosimeters in terms of cumulated activity provide absorbed doses to the salivary glands after application of the S-factor (self-dose) for salivary glands. There were 43 and 127 patients for which dosimeters were readable in the 1.1 GBq group and 3.7 GBq group, respectively. The doses to the salivary glands were approximately 3-times higher in the 3.7 GBq group than in the 1.1 GBq group (Table 3). For the whole group, the dose to the salivary glands per unit administered activity was 0.63 (SD 0.24) Gy/MBq. The ratio of left/right salivary glands cumulated activity was 0.97 (SD 0.15).

**Table 2 table2:** Characteristics of the study population.

Characteristics			1.1 GBq group (n=45)		3.7 GBq group (n=94)		Total (N=139)		*P* value^a^
**Gender, n (%)**									.24
	Women	35 (78)		64 (68)		99 (71.2)			
	Men	10 (22)		30 (32)		40 (28.8)			
Age (years), mean (SD)			47.16 (13.86)		47.02 (14.36)		47.07 (14.15)		.96
BMI, mean (SD)			26.88 (5.93)		27.14 (6.12)		27.06 (6.04)		.82
**Histology, n (%)**									.02
	Follicular	2 (4)		18 (19)		20 (14.4)			
	Papillary	43 (96)		76 (81)		119 (85.6)			
**pTNM^b^ staging, n (%)**									<.001
	Tx-T2	44 (100)		59 (63)		103 (74.6)			
	T3	0 (0)		33 (35)		33 (23.9)			
	T4	0 (0)		2 (2)		2 (1.5)			
	Nx-N0	38 (84)		40 (43)		78 (56.1)			
	N1	7 (16)		54 (57)		61 (43.9)			
**TSH^c^ elevation protocol, n (%)**									<.001
	L-thyroxin replacement stop	0 (0)		49 (52)		49 (35.2)			
	rTSH^d^	45 (100)		45 (48)		90 (64.8)			
**Thyroid remnant tissue, n (%)**									.07
	No	29 (64)		45 (48)		74 (53.2)			
	Yes	16 (36)		49 (52)		65 (46.8)			
**Family history of thyroid cancer, n (%)**									.66
	No	37 (82)		80 (85)		117 (84.2)			
	Yes	8 (18)		14 (15)		22 (15.8)			
**History of systemic disease, n (%)**									.19
	No	31 (69)		66 (70)		97 (69.8)			
	Type 2 diabetes	3 (7)		2 (2)		5 (3.6)			
	Dyslipidemia	3 (7)		3 (3)		6 (4.3)			
	Diagnosed hypertension	6 (13)		22 (23)		28 (20.1)			
	Sjögren syndrome	0 (0)		1 (1)		1 (0.7)			
	Brain tumors	1 (2)		0 (0)		1 (0.7)			
	Other	1 (2)		0 (0)		1 (0.7)			
**History of salivary dysfunctions, n (%)**									.15
	No	41 (91)		91 (97)		132 (95.0)			
	Yes	4 (9)		3 (3)		7 (5.0)			
Delay between surgery and RAI^e^ therapy (months), mean (SD)			4.98 (5.15)		3.69 (3.09)		4.11 (3.91)		.07

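### The unadjusted paired T0–T6 tests cannot separate a 131I effect from any temporary effect of L-thyroxine withdrawal, which was present at T0 in 49/94 patients at 3.7 GBq and 0/45 at 1.1 GBq

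*Protocol article*

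**What the plan says.** The Study Design section says that "START is a prospective self-controlled study". No group without 131I is described, so the T0 visit is the within-patient reference. The section on the enrollment visit places T0 "on the day of treatment, approximately 2 months after surgery", with saliva and questionnaires collected before 131I is given.

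Planned Analyses gives the T0–T6 analysis in one sentence: "Paired comparison tests will be used to assess differences in data between T0 and T6". No stratum, restriction or covariate is attached to it. Regression covariates are chosen by a screen: "All factors significant at a 10% threshold in univariate analyses using different regression models" go forward to the multivariate models. The candidate list includes the stimulation protocol: "pathological tumor-node-metastasis staging, thyroglobulin stimulation protocol, salivary comorbidities". Repeated measurements are handled by "The mixed regression models, adjusted for confounders, performed to investigate the temporal evolution for the different outcomes", with a random intercept and a first-order autoregressive structure. The fixed-effect terms are not listed.

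Table 2 has a row for "L-thyroxin replacement stop" under the TSH elevation protocol: 0 of 45 at 1.1 GBq, 49 of 94 (52%) at 3.7 GBq and 49 of 139 (35.2%) in all, P<.001. The other 90 patients had rTSH, 45 in each activity group.

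**The concern.** Self-control removes patient traits that are the same at both visits. It does not remove a state that is present at one visit and absent at the other. TSH elevation is preparation for 131I and T0 is the day 131I is given, so the 49 withdrawal patients gave their reference values while off replacement. If that state affects a score and has resolved by T6, its resolution appears in the paired change and cannot be told apart from an effect of 131I.

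All 49 patients are in the 3.7 GBq group. The within-patient change in that group is exposed, and so is any comparison of change between the two activities, which is close to the question the study asks. The endpoints at stake are the secondary ones defined as change from T0: quality of life, nutrition, anxiety and depression, and saliva composition.

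**Working it through.** **1. The plan's own figure.** From Table 2: 49/139 = 0.353, 49/94 = 0.521, 0/45 = 0. Pearson chi-square on 0/45 against 49/94 is 36.2, P = 1.8 × 10⁻⁹, which agrees with the printed P<.001.

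**2. Bias of the unadjusted paired change.** Let τ be the true mean T0–T6 change due to 131I, p the share of patients withdrawn, and d the shift that withdrawal causes in a T0 value. Assume the shift has gone by T6. Then

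E(T6 − T0) = τ − p·d.

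The bias has size p·d and the opposite sign to the shift:
- whole cohort: 0.353d
- 3.7 GBq: 0.521d
- 1.1 GBq: 0
- difference in change between activities: 0.521d − 0 = 0.521d

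For assumed shifts of 2, 5 and 10 points this is 0.7, 1.8 and 3.5 points in the cohort, and 1.0, 2.6 and 5.2 points at 3.7 GBq.

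**3. Effect on the test.** Set τ = 0 and express d in SDs of the paired change. By normal approximation the two-sided 5% test has non-centrality p·d·√N / √(1 + p(1 − p)d²). Rejection rates are:

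| assumed d (SD) | all 139 | 3.7 GBq, n = 94 | difference in change, 45 vs 94 |
|---|---|---|---|
| 0.1 | 7% | 8% | 6% |
| 0.2 | 13% | 17% | 9% |
| 0.3 | 24% | 32% | 14% |
| 0.5 | 52% | 69% | 30% |
| 0.8 | 87% | 96% | 61% |

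These rows show sensitivity to d. They are not estimates for this study.

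**4. Whether listing the protocol as a covariate helps.** There are three cases.
- *Paired test:* it takes no covariate, so the listing has no effect.
- *Mixed model on levels, protocol as a main effect only:* with Y = a + b·visit + c·W + patient intercept + error (W = 1 if withdrawn), the term c·W is the same at both visits and cancels from the change. The visit coefficient still targets τ − p·d.
- *Regression of the change itself on W:* here a main effect does adjust the change, provided activity is also in the model. Without it, the W coefficient compares the withdrawn, τ(3.7) − d, with the rTSH patients, ½τ(1.1) + ½τ(3.7). It therefore estimates −d + ½[τ(3.7) − τ(1.1)], so part of the activity effect is absorbed.

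**5. What can be estimated.** No 1.1 GBq patient was withdrawn, so the protocol effect is identified only within the 3.7 GBq group (49 against 45). The pooled rTSH set is 45/90 = 50% 3.7 GBq, against 94/139 = 68% in the cohort. A pooled rTSH change therefore describes a lower-activity mix.

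**6. Precision.** Standard error ratios on enrolled numbers: √(94/45) = 1.45 within 3.7 GBq, and √(139/90) = 1.24 for all rTSH patients against all patients. The smallest paired change detectable with 80% power is 0.238 SD with 139 patients and 0.295 SD with 90.

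**The case against.** Several points on the other side stand.

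- **The primary endpoint is not affected.** It is composite status at T6 against fixed flow cut-offs, and the sample size compares proportions between activity groups. Neither uses a change from T0.
- **Size and direction are not in the documents.** A reader might infer that recovery from withdrawal hides a real 131I-related decline. That needs withdrawal to worsen T0 values and patients to be back on replacement by T6; the article states neither. The T0 saliva and dryness data give no sign of worsening in the group that holds every withdrawal patient. In Table 2 unstimulated saliva is higher at 3.7 GBq (4.12 against 3.13, P=.02), as is stimulated saliva (11.12 against 9.65, P=.07). Dry mouth is 17% against 20%, and normal OSDI 86% against 79%. This does not exclude a shift, because the 3.7 GBq column mixes both protocols and the groups differ in stage and histology. It does weaken the case for salivary outcomes.
- **The plan does not say that the whole T0–T6 change is due to 131I.** It says only that differences will be assessed, and it assigns adjusted inference to the regression models.
- **The variable is already collected and named as a candidate.** The fixed-effect terms are not given, and an article may leave interactions to a fuller plan. If change itself is regressed, a main effect can suffice. The 10% screen would usually keep a large effect: with 49 against 90 patients, a 0.5 SD difference in change passes about 88% of the time. At 0.3 SD it passes about half the time, when the cohort bias would be about 0.1 SD.

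One thing is not answered. The paired tests are fixed without any adjustment, and a covariate whose imbalance is already known to be 52% against 0% should not depend on a significance screen.

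**Conclusion.** The concern holds for the paired T0–T6 tests and the change-type secondary endpoints. A state present at T0 in 35% of patients, all at the higher activity, is not separated from the 131I effect. The bias in the mean paired change is 0.35d overall, 0.52d at 3.7 GBq and 0 at 1.1 GBq.

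This rests on three assumptions: that withdrawal shifts the outcome at T0 by d, that the shift has gone by T6, and that the rTSH patients were not also withdrawn, as the two table categories imply. The documents give neither d nor its sign, so it cannot be said that the results will be biased by a given amount or towards hiding harm. Nor does the point undermine the primary endpoint or call for an untreated control group. It is a gap in the secondary analyses that can be closed with data already in hand.

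**What to change.** - Keep the stimulation protocol in all T0/T6/T18 change analyses, outside the 10% screen.
- In the mixed models include both visit × activity (or salivary gland dose) and visit × stimulation protocol. State that the protocol term is estimated only within the 3.7 GBq group, from 49 withdrawal and 45 rTSH patients.
- Report the paired T0–T6 change in three strata: 1.1 GBq rTSH (n = 45), 3.7 GBq rTSH (n = 45) and 3.7 GBq withdrawal (n = 49).
- Present the two rTSH strata, by activity and not pooled, as the withdrawal-free estimate alongside the all-patient result.

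**Cost.** This changes analysis wording only; no new data are needed. The 3.7 GBq rTSH estimate has a standard error about 1.45 times that of the full 3.7 GBq group, before losses to follow-up. The stimulation protocol was not randomised within the 3.7 GBq group, so a difference between its two strata may reflect patient selection as well as withdrawal, and the report should say so.
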